#### Sample size calculation

Two randomized intervention studies investigating yoga therapies in cancer patients of comparable type and duration using an intervention condition and a waiting-list control group condition produced intergroup effect size in fatigue self-assessment scales of d = 0.66 [29] and d = 0.51 [18]. Based on the lower effect size of d = 0.50 alpha = 0.05 and Power = 0.80 result in a case number of *n* = 64 per group, i.e. 128 patients in total, for a t-test for independent samples with two-sided testing.

#### Recruitment

Oncological patients from the radiotherapy outpatient clinic and the interdisciplinary oncological therapy outpatient clinic who score high in fatigue screening will be invited to a non-binding event via mail where they will receive further information on the study. If no response is received within a week of the invitations being sent, patients will be contacted again by telephone to clarify any ambiguities. Through this recruitment, we hope to maximize participation rate in the first information event. At the first event, the patients will be explained the purpose and procedure of the study and asked to participate in the study.

#### Randomization

The information events will take place every 4 weeks. The participants of the study will be recruited on each information event. All patients who met inclusion criteria will be asked to participate. Participants who will have signed the consent form and completed the first questionnaire set will be randomly assigned to the IG or CG. To ensure that enough patients will be randomized to the intervention group to perform the intervention, a block randomization procedure will be used. Patients meeting the same information event will form a block. The randomization list with computer-generated numbers will be created by the Institute of Clinical Epidemiology and Biometry of the university of Wuerzburg.

### Second RCT (reminder e-mails)

#### Study design and measurement occasions

After the yoga intervention, all participants are randomly assigned to group “Email” who will get weekly reminder e-mail or to group “NoEmail” who will receive no reminder e-mails. Participants of both groups will receive a practice book and a practice CD. Outcomes will be assessed 6 months after the end of the yoga therapy (T3).

#### Reminder e-mail

Reminder e-mails are used for the second question. The e-mails in the first 12 weeks contain descriptions of the twelve asanas - one asana each week - and an encouragement to practice yoga during this week. The asanas are described analogously to the order of the yoga classes. In the following 12 weeks, the 12 reminder e-mails will be repeated in the same order.

#### Randomization

All participants of the Yoga study will be randomly assigned to the group “Email” or “NoEmail”. A block randomization procedure will be used. Patients assigned to a group (IG or CG) after the information event form a block. The randomization list with computer-generated numbers is compiled by staff members of the interdisciplinary Palliative Medicine Centre.

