#### Study design and measurement occasions

Eligible patients will receive the first set of questionnaires as a baseline assessment (T0). All participants will receive psychoeducation intervention (coping with fatigue). Subsequently, they will be randomized to IG or CG. The IG starts with the yoga intervention 1 week after T0, the CG starts 10 weeks after T0. The yoga intervention will be conducted for 8 weeks plus an additional lesson in the ninth week to give the participants the opportunity to catch up on a missed session. Primary and secondary outcomes will be assessed 10 weeks after the start of yoga intervention (T1) via questionnaires. Participants of the CG will also answer a questionnaire at the begin of the yoga intervention (T1) and at the end of the yoga intervention (T2, this will be used in the second RCT).

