### Statistical analysis

To answer the first research question, analyses of covariance (ANCOVA) will be performed, using fatigue score T1 (primary outcome) as dependent variable, type of treatment (IG vs. CG) as independent variable and fatigue at baseline as covariate. The second research question will be analyzed by including the moderator (e.g. gender, age) and the interaction terms (for example group X gender) in the model.

The third research question will be tested again by using ANCOVA, with fatigue T3 as dependent variable, fatigue after the intervention (IG: T1, CG: T2) as covariate and type of reminder (e-mail vs. no email) as independent variable. The fourth research question will be tested by computing a mediation model using structural equation modeling framework [38, 39].

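### The e-mail RCT is randomised within IG/CG-by-event blocks, but its ANCOVA includes neither factor, so the test may be mildly conservative and lose a little power

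*Protocol article*

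**What the plan says.** Under Second RCT, Randomization, all participants of the yoga study are allocated to Email or NoEmail: "A block randomization procedure will be used". The block is then defined: "Patients assigned to a group (IG or CG) after the information event form a block". Allocation is therefore restricted within each combination of information event and first-RCT group.

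The Statistical analysis section gives the model for research question 3: "The third research question will be tested again by using ANCOVA, with fatigue T3 as dependent variable". Its remaining terms are "fatigue after the intervention (IG: T1, CG: T2) as covariate and type of reminder (e-mail vs. no email) as independent variable". Nothing elsewhere in the article adds IG/CG or the block to this model.

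The article does not give the number or size of the blocks. It says only that "The information events will take place every 4 weeks" (First RCT, Randomization).

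**The concern.** Restricting the allocation within blocks removes differences between blocks from the e-mail comparison, because each block contributes to both arms. A model that ignores the blocks still counts those differences as residual error. The reported standard error then describes a simple randomisation that was not carried out, and it is too large.

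The design gives some reason to expect such differences. The two first-RCT groups reach the e-mail phase at different times since baseline: "The IG starts with the yoga intervention 1 week after T0, the CG starts 10 weeks after T0". Patients in one block also share a calendar period.

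What is at stake is sensitivity. The article's only sample size calculation is for the yoga comparison. An e-mail confidence interval that is wider than the design warrants makes an inconclusive answer to question 3 somewhat more likely.

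**Working it through.** **The plan's own figure.** The Sample size calculation section uses these values: "Based on the lower effect size of d = 0.50 alpha = 0.05 and Power = 0.80 result in a case number of" 64 per group, "128 patients in total, for a t-test for independent samples with two-sided testing". The normal approximation gives 63 per group. The exact t-test gives 63.77, rounded up to 64, with power 0.801. The figure reproduces. It belongs to the first RCT, and below it supplies only N = 128, alpha = 0.05 and a reference effect of 0.50.

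**Assumptions not in the document.** Blocks are balanced 1:1. The share of residual T3 variance lying between blocks (ICC, after adjustment for post-yoga fatigue) is 0, 0.05, 0.10 or 0.20. The e-mail effect is 0.50 residual SD. There is no dropout. Residual variance is set to 1.

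**Formulas.**
- SE reported by the model as written: sqrt(4/128) = 0.1768.
- True SE under blocking: 0.1768 × sqrt(1 − ICC).
- Ratio of reported to true SE: 1/sqrt(1 − ICC).
- True type I error: 2 × [1 − Φ(1.96 × ratio)].
- Power as written: Φ((0.50 − 1.96 × 0.1768)/true SE).
- Power with block modelled: Φ(0.50/true SE − 1.96).

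| ICC | True SE | Ratio | Type I error | Power as written | Power with block |
|---|---|---|---|---|---|
| 0 | 0.1768 | 1.000 | 0.050 | 0.807 | 0.807 |
| 0.05 | 0.1723 | 1.026 | 0.044 | 0.813 | 0.827 |
| 0.10 | 0.1677 | 1.054 | 0.039 | 0.820 | 0.847 |
| 0.20 | 0.1581 | 1.118 | 0.028 | 0.834 | 0.885 |

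**With an IG/CG difference as well.** If the groups also differ by 0.5 residual SD, the model as written carries an extra variance of 0.5²/4 = 0.0625. At ICC 0.20 the ratio becomes sqrt(1.0625/0.80) = 1.15.

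**Check by simulation.** Trials of 128 patients were simulated with blocks of 4, 8 or 16, a covariate correlation of 0.6 and 3,000 runs per scenario. Block was entered as fixed terms.
- ICC 0.05: power rose from 0.79–0.82 to 0.80–0.83.
- ICC 0.10: from 0.80–0.82 to 0.83–0.85.
- ICC 0.20: from 0.82–0.83 to 0.88.
- ICC 0.20 with a 0.5 SD group difference: from 0.81–0.82 to 0.88.
- Adding IG/CG without block recovered only about 0 to 2.5 points.

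**Random or fixed block terms.** In a further simulation (blocks of 4 or 8, no dropout), a random block intercept gained about 2, 2–4 and 5–7 power points at ICC 0.05, 0.10 and 0.20, and lost essentially nothing at ICC 0. Fixed block terms were less safe. With blocks of 4, 25% dropout (assumed) and ICC 0, they lost about 5 points. At ICC 0.05 with the same block size and dropout, power fell from 0.669 without block to 0.631 with it.

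**The case against.** The strongest reply is that little is at risk. Question 3 is secondary, the error is on the safe side, and its size rests on ICCs and block sizes that the document does not give. There are also reasons to expect a low ICC. The covariate is measured after the yoga course and so absorbs block differences present by then, and T3 follows six months of individual practice. All of this stands, and it is why the point is small.

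A second reply is that an article condenses its analysis plan, and randomisation factors may appear in the full document. That would answer a complaint about missing detail. Here, however, the article states a blocking rule and a specific covariate set, and the two do not match.

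A third reply is that block adjustment can cost power. This is true of fixed block terms when blocks are small and patients drop out. It does not apply in the same way to a random intercept, although the intercept brings little when its estimated variance is near zero.

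Three stronger readings are tempting but not supported:
- A reader might infer that the e-mail result could be biased or falsely positive. Balanced blocks leave the estimate essentially unchanged, and the type I error lies at or below 5%.
- A reader might infer that taking the covariate at T1 in the IG and at T2 in the CG distorts the comparison. Both are labelled post-intervention values, and blocking within IG and CG balances any timing difference across the e-mail arms.
- A reader might equate a block with a yoga class. That is plausible, but the article does not say so, and the argument needs only a shared group and period.

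**Conclusion.** The concern holds in a limited form. The e-mail allocation is blocked by event and first-RCT group, and the stated ANCOVA ignores both. The consequence is a standard error that may be too large and a test that may be conservative. Over the assumed ICC range of 0 to 0.20, the overstatement runs from nothing to about 12%, or about 15% if IG and CG also differ by half a residual SD. The power loss runs from nothing to about 5–7 points. These figures assume 128 patients, balanced blocks and complete follow-up. At an ICC of 0.05, the loss is only 1–2 points. This is a modest efficiency gain on a secondary question, to be considered rather than required.

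**What to change.** In the question 3 fatigue ANCOVA, add IG/CG as a fixed factor and the randomisation block (information event by group) as a random intercept. Use the same terms in any e-mail comparison of exercise frequency. Specify a random intercept rather than fixed block terms, for the reason shown above. The block term matters most, since IG/CG alone recovers little.

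The change takes about one sentence in the Statistical analysis section and needs no new data, because event and group are known from the allocation. The cost is slightly more analysis work, with little or no gain if block variance proves near zero. Fixing the terms in advance also avoids a later choice between adjusted and unadjusted results.

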### Outcomes, ethics, data management and statistics

#### Outcomes and other measures

Outcomes will be assessed using patient questionnaires or will be extracted from the patient-documentation system. Unless otherwise specified, all outcomes are recorded at all measurement times (T0, T1, T2, T3).

#### Primary outcome: self-reported fatigue

Self-reported fatigue will be assessed using the German version of EORTC QLQ-FA13 13 Items (European Organization for Research and Treatment of Cancer - Quality of Life Questionnaire – Fatigue) [30]. This questionnaire can be used in all tumor diseases in all stages and phases of the disease and in all areas of treatment (chemotherapy, radiation, surgery) or care (acute care, rehabilitation, aftercare or palliative care) [31]. Fatigue is measured using 13 items. Response categories of all items are ‘not at all’, ‘a little’, ‘quite a bit’, and ‘very much’, coded with scores from 1 to 4. All Items are summed up to one fatigue score. The scores range from 0 to 100. Higher values indicate a higher level of fatigue symptoms. The internal consistency for the German version was good with Cronbach’s alpha values ranging from .79–.90 [30, 32].

#### Secondary outcomes

##### Depression

The Patient Health Questionnaire (PHQ-9) will be used to assess depression. The 9 items assess depression symptoms according to DSM-IV/DSM-V and are scored on a 4-point Likert scale (0 = not at all, 1 = several days; 2 = more than half of the days; 3 = nearly all days). All items are summed up to one sum score, ranging from (0–27). Higher values indicate higher depression. The internal consistency for the PHQ-9 proved to be good with Cronbach’s α = 0.79 for cancer patients [33].

##### Quality of life

The EORTC QLQ-C15-PAL is a short form [34] of the QLQ-C30 for palliative care settings. The 15 items of the questionnaire assess nine categories: physical function, emotional function, global QoL, pain, fatigue, appetite, dyspnea, constipation, and sleep. The four response categories are coded with scores from 1 to 4 (1: not at all; 2: a little; 3: quite a bit; 4: very much) and are transformed to a 0–100 scale range.As an exception, global QoL is scored from 1 (very poor) to 7 (excellent). A higher score represents better function and QOL, while for symptom scale, it indicates greater symptom burden.

##### Symptom assessment

The German version of the Edmonton Symptom Assessment Scale (ESAS) [35] will be used to assess symptom severity. The nine symptoms pain, fatigue, nausea, sadness, anxiety, drowsiness, appetite, general condition and shortness of breath are assessed on a numerical rating scale from 0 = none to 10 = worst possible. Higher values in the summed scale score indicate high symptom burden. The internal consistency according to Cronbach’s alpha range between 0.67–0.73 [35].

##### Distress thermometer

The distress thermometer is used to measure psychosocial stress. It uses a numeric rating scale ranging from 0 (no distress) to 10 (extreme distress) and is widely used in clinical practice [36]. A cut-off value of ≥5 is referred to as high distress. Both the dichotomous classification and the sum score of the district thermometer are to be recorded in the study. As a short screening instrument, the Distress Thermometer is well suitable for identifying high loads recorded by Hospital Anxiety and Depression Scale > 11 (AUC values 0.71–0.76) [36].

##### Sense of coherence

The German version of the short form of Sense of Coherence Scale (SOC L9) [37] will be used to record the sense of coherence. This is a reliable, valid and economic alternative short form of the SOC developed by Antonovsky (1983). The 9 items are scored on an 8-point Likert scale. Response formats vary between items. Higher values indicate a high degree of coherence, whereby age- and gender-dependent norms must be applied. The internal consistency of the SOC L9 can be rated as good (Cronbach’s alpha = .87) [37].

##### Sociodemographic and health data

The following socio-demographic data will be assessed at T0: age, gender, marital status, number of children, level of education, professional status. Individual coping with the tumor disease, treatment status and use of analgesics and psychopharmaceuticals will be assessed at each measurement occasion. In addition, previous experience with yoga and expectations of the participants on yoga will be asked at T0.

##### Program evaluation and training time

At the end of the intervention (IG: T1; CG: T2), participants comprehensibility and applicability of the yoga theory and psychoeducation as well as subjective benefit will be assessed on a scale from 0 (not at all) to 3 (very). Furthermore, the current scope of the exercise duration (yoga) and the application frequency of the recommendations for handling fatigue will be measured at T1(IG)/T2(CG) and T3(IG and CG). Reasons for continuing or ending yoga practice are documented.

### Data management and confidentiality

In order to guarantee the confidentiality of data, the data will be pseudonymized using an allocation list. A research code will be assigned to each study participant so that only the code and no personal data will be used on all questionnaires. All questionnaires will be kept in locked cabinets and/or password protected computers. The allocation list will be only accessible to the data manager of the University Hospital Wuerzburg responsible for allocating medical data. The allocation list is deleted after the end of the study. It will contain the name, address, date of birth, SAP research number and contact data of the patients. During the period of this assignment, the research data will be considered “personal data” and the data protection laws are to be complied. The questionnaires will be scanned by the software EvaSys. The data will be exported to statistical programs for further statistical analysis. The data manager will compare the transferred data of the questionnaires item by item with the original questionnaires. Additional data, such as treatment duration and intensity, will be taken from the electronic patient file. The data manager will also advise on storage, back up and archiving of data to ensure databases are regularly backed up to ensure data is safeguarded from accidental loss. The study master file and all study documentation will be archived for at least 10 years.

### Statistical analysis

To answer the first research question, analyses of covariance (ANCOVA) will be performed, using fatigue score T1 (primary outcome) as dependent variable, type of treatment (IG vs. CG) as independent variable and fatigue at baseline as covariate. The second research question will be analyzed by including the moderator (e.g. gender, age) and the interaction terms (for example group X gender) in the model.

The third research question will be tested again by using ANCOVA, with fatigue T3 as dependent variable, fatigue after the intervention (IG: T1, CG: T2) as covariate and type of reminder (e-mail vs. no email) as independent variable. The fourth research question will be tested by computing a mediation model using structural equation modeling framework [38, 39].

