Follow-up findings for mind-body interventions dealing with fatigue vary widely. While some randomized controlled trials (RCT) show significant effects in fatigue following a mind-body intervention, but no longer after 3 months [12, 20], others found no effects immediately after an intervention, but 3 months later [21]. Lengacher et al. [22] showed significant reduction of fatigue compared to a CG after the intervention and also in a catamnesis 6 weeks later [22]. An observational study showed significant long-term effects of mind-body intervention regarding depression and general mood after 1 year, but no long term effects regarding fatigue [23].

The yoga therapy intervention we used in our study was already evaluated in previous studies. Using a randomized controlled design, Lundt et al. [24] showed that this kind of yoga therapy significantly reduce anxiety in cancer patients with mean to high effect size (d = 0.75). However, no effects significant effects were found for fatigue and depression [24]. In an observational, catamnestic study without control group based on the study above, 6 months after yoga intervention significant changes in fatigue (d = 0.32), anxiety (d = 0.33) and depression (d = 0.40) were observed compared to baseline measurement [25].

An important moderator of the effect on fatigue is frequency in exercising of the patients during and after the intervention [19, 21]. To improve exercise frequencies, participants often receive exercise CDs and/or exercise books at the end of yoga intervention [11, 16, 18–20]. Documentation of their daily exercise duration in addition to the exercise CD has also shown to be helpful for the sustainability of the effects [21]. In the area of oncological complementary therapy, supporting participants via phone calls at weekends within an ongoing mind-body intervention helps to maintain the continuity of the exercises [26]. In the medical context, daily reminder e-mails increased adherence to medication [27, 28]. However, there are no comparable studies on mind-body procedures to improve fatigue symptoms that use weekly reminder e-mails to promote sustainable effects.

In this study, the following research questions will be examined:

Primary research question:
Does an 8-week yoga intervention (IG) reduce self-reported fatigue symptoms directly after the intervention compared to a waiting-list control group (CG)? We expect an effect of d = 0.50 in favor of the IG.

Secondary research questions

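### The primary ANCOVA and the sample size assume independent patients although yoga appears to be taught in classes, so the 5% level is not protected if outcomes correlate within a class

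*Protocol article*

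**What the plan says.** All references are to the Protocol article.

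- **Primary model** (Statistical analysis): an ANCOVA "using fatigue score T1 (primary outcome) as dependent variable, type of treatment (IG vs. CG) as independent variable and fatigue at baseline as covariate". There is no term for class, teacher or information event.
- **Sample size** (Sample size calculation): "Based on the lower effect size of d = 0.50 alpha = 0.05 and Power = 0.80 result in a case number of" 64 per group, "i.e. 128 patients in total", "for a t-test for independent samples with two-sided testing". No design effect, class size or baseline correlation enters.
- **Randomisation** (First RCT, Randomization): "Patients meeting the same information event will form a block". The reason is given as: "To ensure that enough patients will be randomized to the intervention group to perform the intervention, a block randomization procedure will be used". Information events are held every 4 weeks.
- **Delivery**: the Reminder e-mail section speaks of classes: "The asanas are described analogously to the order of the yoga classes". The Yoga-intervention section has certified teachers, in the plural, delivering a fixed sequence of exercises.
- **Timing** (First RCT, Study design and measurement occasions): the IG starts yoga 1 week after T0 and the CG 10 weeks after T0. The CG answers its T1 questionnaire as its own yoga begins.

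**The concern.** A minimum number of IG patients per event is needed only if yoga is taught to a group. The four-weekly events and the common start one week after T0 point the same way. Patients who share a class also share a teacher, a timetable and each other's company, and their fatigue scores at T1 may be correlated as a result. CG patients have shared no yoga class by then. This is a partially nested design: clustered in one arm, unclustered in the other.

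The stated ANCOVA computes its standard error as if all 128 patients were independent. Under any positive within-class correlation that standard error is too small, the interval too narrow and the p-value too low. This is the single primary test, and the Discussion ties a positive result to introducing yoga into routine practice, so a raised false-positive rate would matter.

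**Working it through.** **1. The protocol's figure.** Inputs from Sample size calculation: d = 0.50, two-sided alpha 0.05, power 0.80, equal groups. The noncentral t distribution gives power 79.5% at 63 per group and 80.15% at 64. The stated 64 per group is reproduced. The arithmetic is right, and only the independence assumption is open.

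**2. Variance with clustering in the IG only.** Let m be the class size and ICC the within-class correlation. The protocol gives neither, so both are assumed. The IG mean has its variance multiplied by 1 + (m−1)·ICC and the CG mean by 1. With equal groups the variance of the difference is multiplied by

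V = [1 + 1 + (m−1)·ICC]/2 = 1 + (m−1)·ICC/2.

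**3. Actual alpha and power at 64 per group.** Alpha = 2·[1 − Φ(1.96/√V)]. Power is from the noncentral t with effect 0.50/√V, which is the protocol's unadjusted t-test basis. For m = 8, V = 1 + 3.5·ICC:

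| ICC | V | √V | Actual alpha | Power, unadjusted |
|---|---|---|---|---|
| 0.01 | 1.035 | 1.017 | 5.4% | 79% |
| 0.02 | 1.070 | 1.034 | 5.8% | 77% |
| 0.05 | 1.175 | 1.084 | 7.1% | 74% |
| 0.10 | 1.350 | 1.162 | 9.2% | 68% |

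Over ICC 0.01 to 0.10, alpha runs from 5.3% to 8.0% for m = 6, and from 5.6% to 11.5% for m = 12.

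**4. Does baseline adjustment repair alpha?** The stated ANCOVA was simulated under no treatment effect: 8 events, each with 8 IG patients in one class and 8 CG patients, an assumed baseline correlation of 0.5, and ICC taken as a share of the variance left after baseline (20,000 runs per setting). Type I error was 5.2%, 5.9%, 7.0% and 9.0% at ICC 0, 0.02, 0.05 and 0.10. It does not.

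**5. Does the planned ANCOVA keep 80% power?** Adjustment for a baseline score with correlation r multiplies the variance by 1 − r². It offsets V when V·(1 − r²) = 1, that is, r = √(1 − 1/V). For m = 8 and ICC 0.02, 0.05 and 0.10 this gives r = 0.26, 0.39 and 0.51. With an assumed r = 0.5, power at 128 patients is about 88%, 85% and 80%. These figures assume that the test uses the correct standard error and full degrees of freedom.

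**6. The omitted information event.** In the same simulation, with no class effect but an event effect shared by both arms (5% of the variance), type I error was 4.5%. With ICC 0.05 and event variances of 0.02 and 0.05, it was 7.1% and 6.9%. Leaving out the event is slightly conservative on its own and does not cancel the class effect.

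**The case against.** The strongest reply is that the size of the problem rests on two numbers the protocol does not give. At ICC 0.01 alpha is about 5.4%, which is trivial. A constant exercise sequence and an individually self-reported outcome are both compatible with a small ICC, and the 9% figure needs the top of the assumed range. This stands: the omission is certain, its size is not.

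Three stronger readings may tempt a reader, and the document does not support them.

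- *The trial has less than 80% power.* The reduced figures belong to the unadjusted t-test. The planned analysis adjusts for baseline fatigue, and a moderate correlation recovers the loss. That correlation is not stated either, so a shortfall is neither shown nor excluded.
- *Ignoring the randomisation block also makes p-values too small.* It acts in the other direction, as step 6 shows.
- *Each event forms exactly one class with one teacher.* This is the natural reading of the blocking rationale, but the text does not say so, and a catch-up lesson in week nine leaves membership somewhat open.

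It can also be said that a condensed article leaves random-effect structure to a full analysis plan. That moderates the point but does not remove it, because the article states the primary model and the basis of the sample size outright.

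Finally, the remedy has a real price. Classes of 8 give 64/8 = 8 IG classes. If the degrees of freedom fell to the lower bound of 7, power on the unadjusted basis at ICC 0.05 would be about 61% rather than 74%. The true value lies between the two.

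**Conclusion.** The point holds in conditional form. The stated primary model and sample size assume independence for an intervention that the text implies is delivered in classes to one arm only. If outcomes correlate within class, the nominal 5% level is not protected. With an assumed class size of 8, the actual level is about 5.4%, 6%, 7% and 9% at ICC 0.01, 0.02, 0.05 and 0.10. The stated 80% power is correct only for zero within-class correlation and no credit for baseline. Whether the planned ANCOVA reaches 80% cannot be decided from the document. The direction of the error in alpha is firm for any positive ICC; its size depends on the assumed class size and ICC.

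**What to change.** 1. Record prospectively which class and which teacher each patient had.
2. Make the primary analysis a partially nested linear mixed model for T1 fatigue, with T0 fatigue, arm and information event, and a random class effect in the IG only. Use Satterthwaite or Kenward-Roger degrees of freedom and report the estimated ICC. Including the event aligns the model with the randomisation and can gain precision; it is not there to correct alpha. If each event yields exactly one IG class, check beforehand that event and class effects can both be estimated.
3. In Sample size calculation, state that the 80% power assumes no within-class correlation, and give the range of power by class size, ICC and baseline correlation.

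Cost: one extra item of data per patient and a change of analysis wording. The interval will be wider, the effective degrees of freedom fewer with only about eight IG classes, and the stated power less favourable. No extra patients are needed for this change.

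### The primary ANCOVA omits the information event within which patients are randomised, which is valid but may be mildly conservative

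*Protocol article*

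**What the plan says.** - **Primary model.** Statistical analysis in the protocol article gives T1 fatigue as the dependent variable, with "type of treatment (IG vs. CG) as independent variable and fatigue at baseline as covariate". Gender, age and the other moderators enter only for the second research question.
- **Randomisation.** Under Randomization (first RCT): "Patients meeting the same information event will form a block". Events are held every 4 weeks. Neither the number of events nor the attendance per event is given. No stratification by treatment status, clinic or tumour type is described.
- **Timing of baseline data.** The same section states: "Participants who will have signed the consent form and completed the first questionnaire set will be randomly assigned to the IG or CG". Everything in the T0 questionnaires therefore precedes allocation.
- **Treatment status.** Under Sociodemographic and health data: "treatment status and use of analgesics and psychopharmaceuticals will be assessed at each measurement occasion". Status at T0 is thus available for every patient.
- **Eligibility.** Study-setting and eligibility criteria requires patients to be under treatment at one of two outpatient clinics when screened.
- **Sample size.** The calculation is "for a t-test for independent samples with two-sided testing", at d = 0.50 with "alpha = 0.05 and Power = 0.80", giving 64 "per group, i.e. 128 patients in total".

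**The concern.** When allocation is restricted within blocks, the analysis would normally reflect those blocks. If patients from one event tend to be more fatigued at T1 than patients from another, given baseline, that variation is largely balanced between arms by the design. A model without the event still counts it as residual noise. The standard error is then larger than the design warrants, and some power is given away.

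A second, weaker point concerns T0 treatment status. It is recorded before randomisation, is not balanced by design, and could predict T1 fatigue beyond the baseline score. If so, adjusting for it would gain some precision. It would also have to be pre-specified, since adding it after seeing an imbalance in the baseline table would look data-driven.

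At stake is efficiency in the primary comparison, not its validity.

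**Working it through.** **1. The plan's own figure.** For a two-sided t-test with d = 0.50 and alpha 0.05, the noncentral t gives power 0.7952 at 63 per group and 0.8015 at 64. The stated 64 per group is reproduced.

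**2. Power of the ANCOVA, with and without further terms.** Assumed, because the documents do not give them: the correlation r between baseline and T1 fatigue, the share s of remaining variance that the added terms explain, and about 12 degrees of freedom for event and status together.

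- Residual variance: V = (1 − r²)(1 − s)
- Noncentrality: 0.50/√V × √(64/2)
- Degrees of freedom: 125 for baseline only, 113 with the added terms

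Example at r = 0.5, baseline only: V = 0.75, noncentrality = 0.50/0.866 × 5.657 = 3.27, power 0.900. With s = 0.10: V = 0.675, noncentrality = 0.50/0.822 × 5.657 = 3.44, power 0.927.

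| r | baseline only | s = 0 | s = 2% | s = 5% | s = 10% |
|---|---|---|---|---|---|
| 0.3 | 0.837 | 0.836 | 0.844 | 0.855 | 0.873 |
| 0.5 | 0.900 | 0.899 | 0.905 | 0.913 | 0.927 |
| 0.6 | 0.939 | 0.939 | 0.943 | 0.949 | 0.959 |

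The largest gain is 0.873 − 0.837 = 3.6 points. The standard error falls by 1 − √(1 − s), which is 1.0%, 2.5% and 5.1% for s = 2%, 5% and 10%.

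**3. Simulation of validity and power.** Settings: 4000 runs, 128 patients, 12 events with arms balanced within event, r = 0.5, an event effect common to both arms, a 50:50 status variable, and events fitted as fixed effects. The first column is the share of residual variance explained by event and by status, each.

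| Share each | Type I error, baseline only | Power, baseline only | Power, + event | Power, + event + status |
|---|---|---|---|---|
| 0 | 0.049 | 0.894 | 0.891 | 0.887 |
| 2% | 0.048 | 0.897 | 0.896 | 0.899 |
| 5% | 0.043 | 0.892 | 0.903 | 0.916 |
| 10% | 0.043 | 0.911 | 0.927 | 0.945 |

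The baseline-only test never exceeds its nominal level by this check and drifts slightly below it when events matter. The simulation error of a rate near 0.05 is √(0.05 × 0.95/4000) = 0.003. Adding both terms changes power by −0.7, +0.2, +2.4 and +3.4 points. Adding the event alone changes it by −0.3, −0.1, +1.1 and +1.6 points.

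**4. Treatment status alone.** Let p be the share on treatment at T0 and δ the difference in T1 fatigue given baseline, in SD units. The share of residual variance removed is p(1 − p)δ²/(1 − r²). Assume p = 0.9 (in line with the eligibility rule), r = 0.5 and δ = 0.3 to 0.7:

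- δ = 0.3: 0.09 × 0.09/0.75 = 1.1%
- δ = 0.7: 0.09 × 0.49/0.75 = 5.9%

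That is about 1 to 6%. The 95% range of chance imbalance between arms is 1.96 × √(2 × 0.09/64) = ±10 percentage points, which corresponds to 0.03 to 0.07 SD in the estimate. This is not a further cost on top of the variance above: the unadjusted standard error already allows for it.

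**The case against.** The strongest case against is that nothing here is wrong. The plan already adjusts for the baseline value of the outcome, which is probably the strongest predictor. The sample size rests on an unadjusted t-test, so the planned ANCOVA has power of about 0.84 to 0.94 for r between 0.3 and 0.6 before dropout. The source is also a condensed article, and a block term may stand in an analysis plan that is not shown. All of this stands. What remains is that the article states its primary model explicitly, and the stated model leaves out the unit of restriction.

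A reader might infer more, in three ways that the documents do not support.

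- **That the standard errors are invalid.** With an event effect common to both arms, the error runs in the conservative direction and is small.
- **That adjustment is free and guards against imbalance.** Randomising within events already roughly balances the arms by event, so an event term adds little protection. If the terms predict nothing, there is a slight loss.
- **That omitting treatment status costs a great deal.** Assuming 30 to 50% on treatment, the formula in step 4 gives roughly 3 to 16% of residual variance. That share sits poorly with the requirement to be under treatment at screening. Some patients may have finished by T0, so the true share is unknown, but p(1 − p) is near its maximum in that range. The 0.3 to 0.7 SD effect is also only an assumption: the article's Background gives a prevalence of fatigue during treatment, not a comparison with patients off treatment at equal baseline fatigue.

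**Conclusion.** The point holds as a modest efficiency improvement. The stated primary model leaves out the information event, although allocation is made within it. The analysis remains valid: simulated type I error was 0.043 to 0.049. The expected total gain from adding event and treatment status is about 0 to 4 power points at 64 per group, with a loss of under 1 point if neither predicts T1 fatigue. The upper end needs the added terms to explain about 10% of residual variance or more, which the documents neither support nor exclude. The event alone gained at most 1.6 points in the simulation.

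These figures rest on assumed baseline correlations of 0.3 to 0.6, about 12 events, and an event effect shared by both arms. The treatment-status part is a secondary suggestion only, because both the share on treatment at T0 and its prognostic strength are unknown. Neither the sample size nor the primary conclusion is at risk.

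**What to change.** Pre-specify the primary model as T1 fatigue on group and T0 fatigue, with the information event included. A random effect is preferable, because events every 4 weeks may produce many small blocks and fixed effects would use one degree of freedom for each event after the first. Keep the baseline-only ANCOVA as a sensitivity analysis.

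Optionally, add T0 treatment status as a pre-specified covariate. The article does not define its categories, so the coding must be written down before the data are seen. Treatment status at T1 must not be used, because it is measured after randomisation.

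The change is to the analysis wording only. It needs no new data and no more patients, and costs one or two degrees of freedom with the event as a random effect. If a separate analysis plan already contains the event term, nothing further is needed beyond making the two texts agree.
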